### Ethics statement

This trial, registered at ClinicalTrials.gov (NCT05997225), was approved by the Montefiore Einstein IRB (#2023–14980). All participants included in the study provide informed consent before participating, and the study follows the Declaration of Helsinki and regulatory guidelines. This manuscript complies with SPIRIT guidelines, which promote transparent reporting of clinical trial protocols, including trial design, enrollment, interventions, and planned outcomes.

## Discussion

This novel study aims to test an Enhanced Care opt-out smoking treatment model tailored to the unique needs of this high-risk cohort, with a focus on overcoming the significant challenges of engaging individuals who smoke in treatment. Addressing these engagement challenges is critical to ensuring the success of cessation efforts, particularly for vulnerable groups like FDNY-WTC responders. Smoking remains the leading preventable cause of death and disease in the U.S., accounting for nearly 500,000 deaths annually, or one in five deaths [51, 52]. Although roughly 55% of people who smoke cigarettes try to quit each year, fewer than 10% succeed [53, 54]. Despite substantial declines in smoking rates among FDNY responders over the past two decades, a subset continues to smoke, facing heightened risks of lung function decline, respiratory disease, and lung cancer.

Among FDNY-WTC responders, the health effects of smoking have been exacerbated by exposure to the WTC disaster. Responders experienced an average 20% loss in lung function following 9/11, with over 20% developing new-onset obstructive airways disease [55]. Studies within the FDNY-WTCHP cohort have demonstrated that lung function decline is most pronounced among individuals who currently smoke, while smoking cessation significantly mitigates this decline [6]. 

The Enhanced Care intervention incorporates several innovative strategies to overcome common barriers to cessation success. The opt-out enrollment model addresses low treatment engagement by enrolling participants unless they actively decline, a tactic proven effective in improving adherence in other chronic disease management contexts, such as colorectal cancer screening [9, 56]. Proactive counseling builds on participants’ LDCT and spirometry findings to deliver personalized, motivational messaging that highlights the immediate and long-term benefits of smoking cessation, leveraging the concept of a “reachable, teachable moment” [5] during periods of heightened health awareness. Such biofeedback interventions have yielded mixed results in motivating behavioral change, with some evidence suggesting potential benefits, particularly when linked to tangible health outcomes [22–27, 57]. No LDCT lung cancer screening program in occupational health has adopted a true opt-out enrollment model, in which services are initiated unless actively declined, despite its alignment with guidelines recognizing high nicotine dependence as a major risk factor. This trial addresses the gap by comparing Standard Care with Enhanced Care to evaluate whether this approach improves enrollment and cessation outcomes in high-risk individuals who smoke.

Additionally, varenicline preloading is offered to all participants to mitigate pre-quit tobacco enjoyment and withdrawal symptoms, supported by evidence from randomized trials showing preloading increases quit rates and reduces cravings [29]. The inclusion of personalized NRT options further supports individualized treatment plans, reflecting best practices recommended by the U.S. Public Health Service [58]. 

The trial faces some potential obstacles. The FDNY-WTCHP cohort is actively followed with numerous opportunities for tobacco cessation treatment and has already achieved substantial success in reducing tobacco use, potentially limiting the magnitude of change detectable with new interventions. The remaining individuals who smoke have been the most challenging to treat. However, the Program’s continued investment in reducing smoking rates to zero underscores the importance of refining and expanding tobacco treatment strategies. Additionally, the design of the Enhanced Care arm may not fully capture its potential impact, as participants must still actively consent to participate despite being proactively contacted by the research team. Nonetheless, the direct comparison of opt-out versus opt-in models is expected to provide valuable insights into strategies for increasing engagement during recruitment that may promote treatment success. The findings may have limited generalizability, as the FDNY-WTCHP population benefits from extensive tobacco cessation resources that are not widely available. Additionally, the enhanced care arm includes additional contact time compared to the standard care arm, which may contribute to differences in outcomes. The bundled intervention, combining opt-out enrollment, biofeedback, and varenicline preloading, presents challenges in isolating the effects of individual components, making it difficult to disentangle the impact of each aspect of the intervention. These factors may limit the feasibility and scalability of the approach in less resource-rich settings. Furthermore, some participants may face challenges with technology, which, along with the virtual nature of the study, could pose additional barriers to engagement and adherence.

This trial has the potential to provide several important benefits, including mitigating the burden of smoking-related diseases such as COPD, cancer, and cardiovascular disease. Additionally, the Enhanced Care model may contribute to improved quality of life and reduced healthcare costs among responders [59]. Findings could inform occupational and LDCT lung cancer screening programs by integrating tobacco treatment initiatives, which can expand access to treatment and counter the misconception that screening eliminates the need to quit smoking [60]. This integration is especially relevant given evidence suggesting that tobacco treatment interventions significantly enhance the cost-effectiveness of LDCT lung cancer screening by reducing smoking-related disease incidence [61, 62].

This study seeks to redefine tobacco treatment by engaging high-risk individuals who smoke and have struggled with traditional methods. By combining opt-out enrollment, biofeedback from LDCT and spirometry, and varenicline preloading, the intervention aligns with CMS recommendations for integrating tobacco counseling into LDCT lung cancer screening [43] and is novel in its application to an occupational cohort. It addresses a critical research gap, targeting a challenging-to-treat population with significant tobacco exposure and health risks. If successful, the Enhanced Care model could reduce smoking-related health burdens and offer scalable strategies to improve treatment outcomes in both occupational and broader populations.

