**Methods:**

The trial includes retired Fire Department of the City of New York (FDNY) responders aged 50 years or older who have a smoking history that satisfies either the National Comprehensive Cancer Network criteria of at least 20 pack-years or a simplified criterion of at least 20 years of smoking. Participants are randomized to either Enhanced Care, featuring opt-out enrollment in tobacco treatment with tailored counseling using biofeedback from chest LDCT and spirometry results, or Standard Care, requiring opt-in enrollment and standard tobacco treatment without biofeedback. Both arms receive a varenicline regimen with 4 weeks of pre-loading. Primary outcomes are treatment enrollment and biochemically verified 7-day abstinence. Factors associated with enrollment and abstinence, including retention, adherence, and quit motivation, will be evaluated.

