## Methods

### Study setting

The FDNY-WTCHP offers responders monitoring exams every 12–18 months, a lung cancer Chest LDCT screening program for high-risk individuals with a 20 pack-year history of smoking, and tobacco treatment services, including free access to medications and counseling. Smoking status and pack-year history have been routinely collected since the 9/11 disaster through standardized self-reported questionnaires administered during regular health monitoring visits as part of the FDNY-WTCHP [28]. The current FDNY-WTCHP treatment protocol includes counseling and nicotine replacement therapies (NRT), with varenicline prescribed as needed. Preloading, where medication is initiated prior to target quit date, is recommended, but not required, to reduce cravings and withdrawal symptoms [29]. 

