### RCT study design

This trial evaluates the effectiveness of an Enhanced Care intervention (opt-out) versus Standard Care (opt-in) in promoting tobacco cessation among retired FDNY-WTCHP responders who are eligible for LDCT lung cancer screening based on their self-reported smoking history. Using a parallel-arm design, the trial compares these interventions among WTC-exposed responders who currently smoke (Fig. 2). The Enhanced Care intervention includes opt-out enrollment in tobacco treatment, in which participants receive services unless they actively decline, tailored counseling with biofeedback based on LDCT scan and spirometry results, and varenicline with preloading, initiated before the target quit date, along with NRT as needed. In contrast, the Standard Care intervention requires opt-in enrollment and offers standard counseling without personalized biofeedback, and varenicline with preloading, initiated before the target quit date.

All participants follow a standardized treatment protocol that includes varenicline preloading for four weeks prior to the target quit date, followed by 12 weeks of varenicline. Counseling sessions are conducted via telehealth at baseline and weeks 2, 4, 8, 12, and 16, with a final follow-up at week 28. Research assessments are completed online at the same time points: baseline and weeks 2, 4, 8, 12, 16, and 28. Nicotine metabolite urine testing is conducted at Quest Diagnostics labs near participants’ homes. Participants receive a $30 gift card for each research visit they complete, which includes a complete questionnaire, a counselor visit, and a urine test. These measures are designed to enhance participation, adherence, and consistency across both intervention groups, supporting a thorough evaluation of factors influencing cessation outcomes.

The primary objectives of the trial are to compare enrollment rates between the Enhanced Care and Standard Care groups (objective 1), to analyze the impact of sociodemographic and clinical factors on enrollment, and to assess program outcomes: retention, adherence to varenicline and counseling, and tobacco abstinence (objective 2). A summary of study activities is described in Table 2.

**Table 2 Tab2:** Patient timeline by treatment arm: Enhanced Care and Standard Care

	Enrollment		Baseline (Week 0)		Week 2		Week 4		Week 8		Week 12		Week 16		Week 28	
	S	E	S	E	S	E	S	E	S	E	S	E	S	E	S	E
Enrollment																

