### Counseling approach

All participants receive seven structured telehealth counseling sessions (via Microsoft Teams) with a certified tobacco treatment specialist. These sessions focus on evidence-based strategies, including problem-solving, skills training, and biofeedback, ensuring fidelity and consistency across study arms while addressing individual needs. Counseling sessions also reinforce adherence to the varenicline regimen (S1).

The counseling approach is informed by a comprehensive checklist adapted from The Manual of Smoking Cessation: A Guide for Counsellors and Practitioners (S2) [48]. Key components include assessing withdrawal symptoms, facilitating action planning, addressing lapse triggers, and reinforcing an identity as someone who has quit smoking. Education on nicotine monitoring and pharmacological aids, combined with biofeedback, ensures participants receive consistent, evidence-based support.

Counseling sessions include building rapport, assessing smoking behaviors and readiness to quit, addressing withdrawal symptoms, and managing barriers to cessation. Participants receive tailored advice on avoiding social smoking cues, restructuring their environment, and developing coping strategies to prevent relapse. Behavioral action plans, goal setting, and progress reviews are integral to each session. Education on the health benefits of quitting, the purpose of nicotine monitoring, and the use of pharmacological aids are also provided. Participants are encouraged to self-record tobacco use, identify reasons for quitting, and engage with social support systems.

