### Enhanced Care arm

In the Enhanced Care arm, counseling integrates biofeedback from participants’ LDCT and spirometry results to create periods of increased health awareness that may enhance receptivity to behavior change [5, 49]. For individuals with LDCT abnormalities (e.g., nodules, bronchial wall thickening, emphysema, chronic obstructive pulmonary disease (COPD), or fibrosis), counseling highlights the benefits of smoking cessation, including the potential resolution of inflammation in ground-glass nodules and a slower progression of disease. Spirometry results indicating accelerated lung function decline or dysfunction are used to highlight the benefits of quitting in slowing disease progression. Participants with normal findings are counseled on long-term health benefits and preventing future complications. Nicotine metabolite results are incorporated to provide additional biofeedback, reinforcing adherence to the treatment program and titrating nicotine replacement medications when necessary. Nicotine replacement medications are added, if necessary, to attenuate break-through withdrawal symptoms and/or to attain complete abstinence. Enhanced Care sessions are structured to last between 30 and 40 min.

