### Standard Care arm

In the Standard Care arm, counseling follows the same structured framework but does not incorporate tailored biofeedback from LDCT or spirometry results. Participants in this arm receive varenicline including preloading. Instead, the sessions focus on general strategies for quitting smoking and maintaining abstinence. Standard care sessions are designed to be brief, typically lasting under 15 min.

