### Pharmacological support

All participants, regardless of study arm, receive a total of 16 weeks of varenicline: preloading for four weeks prior to the participant’s target quit date, followed by 12 weeks of varenicline. Dosing is standard: 0.5 mg daily for three days, followed by 0.5 mg twice daily for days 4 through 7, followed by 1 mg twice daily thereafter. Varenicline preloading is offered to all participants to reduce pre-quit tobacco enjoyment and withdrawal symptoms. Varenicline preloading prior to the target quit date has been shown to reduce the rewarding effects of smoking and increase quit success rates [29]. In both the enhanced and standard care arms, appropriate NRTs are added to varenicline when necessary and substituted in cases of adverse drug events (ADEs) to ensure individual tolerability and safety. Nicotine replacement medications are added, when necessary, to attenuate break-through tobacco withdrawal symptoms and/or to attain complete abstinence.

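### Varenicline preloading is presented as part of the tested Enhanced Care bundle although both arms receive it, and one section gives biofeedback to both arms

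*Protocol article*

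**What the plan says.** **Preloading.** The limitations paragraph of the Discussion reads "The bundled intervention, combining opt-out enrollment, biofeedback, and varenicline preloading, presents challenges in isolating the effects of individual components". The Discussion part of the Abstract, the last paragraph of the Background and the closing paragraph of the Discussion name the same three elements. The Background adds that the trial evaluates this bundled model against standard care. On delivery, the Methods part of the Abstract states "Both arms receive a varenicline regimen with 4 weeks of pre-loading". RCT study design, Standard Care arm, Pharmacological support and the Discussion paragraph on varenicline also give preloading to everyone.

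**Biofeedback.** Counseling approach opens with the seven sessions that all participants receive and continues: "These sessions focus on evidence-based strategies, including problem-solving, skills training, and biofeedback, ensuring fidelity and consistency across study arms". Its second paragraph again names biofeedback as part of the consistent support given. Standard Care arm says that counseling there "does not incorporate tailored biofeedback from LDCT or spirometry results". The Abstract (Methods), RCT study design and Table 2 also withhold it from Standard Care.

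**NRT.** RCT study design describes Enhanced Care as including "varenicline with preloading, initiated before the target quit date, along with NRT as needed" and does not mention NRT for Standard Care. Pharmacological support says "In both the enhanced and standard care arms, appropriate NRTs are added to varenicline when necessary". Enhanced Care arm links nicotine metabolite results to "titrating nicotine replacement medications when necessary".

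**The concern.** A randomized comparison estimates the effect of what differs by assignment. If a component is listed in the tested bundle but is given to both arms, a positive result will be credited to something the trial did not vary. The closing Discussion paragraph already builds its anticipated conclusion on the three-part combination, so the error would pass into the report.

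The biofeedback wording raises a different problem, one of delivery. Consistency and fidelity says that the same tobacco treatment specialist conducts every session in both arms. If that person followed Counseling approach as written, controls would receive an element that is meant to distinguish Enhanced Care. The abstinence comparison would then test a weaker contrast than intended.

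**Working it through.** No calculation applies: the article gives no sample size, power or effect size to reproduce. The check is a comparison, component by component, of every section that assigns it to an arm.

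| Component | Sections treating it as specific to Enhanced Care | Sections giving it to both arms |
|---|---|---|
| Preloading | Named in the bundle: Abstract (Discussion), Background, Discussion (limitations; closing paragraph) | Abstract (Methods), RCT study design, Standard Care arm, Pharmacological support, Discussion (varenicline paragraph) |
| Biofeedback | Abstract (Methods), RCT study design, Table 2, Enhanced Care arm, Standard Care arm, Consistency and fidelity, Measures | Counseling approach |
| NRT | RCT study design (listed for Enhanced Care, not mentioned for Standard Care); metabolite-guided titration in Enhanced Care arm only | Pharmacological support |
| Opt-out versus opt-in enrollment | All sections agree that it differs | None |
| Session length | Enhanced Care arm (30 to 40 min) versus Standard Care arm (typically under 15 min) | None |

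**Preloading.** Every section that describes delivery gives it to both arms; only the descriptions of the bundle make it an Enhanced Care element. Of the three named components, 3 − 1 = 2 differ by assignment. The trial can estimate the effect of those two, with the extra session time, when everyone treated is preloaded. It cannot say what preloading adds, or whether the result would be the same without it. The limitations paragraph says that the components are hard to separate, which presumes that preloading lies inside the contrast. It lies outside.

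**Session length.** This does differ but is not named in the bundle. At the stated lengths the gap is more than 30 − 15 = 15 minutes per session, or more than 7 × 15 = 105 minutes over seven attended sessions.

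**Biofeedback.** Could Counseling approach mean only feedback on nicotine metabolites, leaving the exclusion of LDCT and spirometry results intact? Enhanced Care arm, Consistency and fidelity, and Measures all place metabolite feedback in Enhanced Care too, and the Abstract excludes biofeedback from Standard Care without qualification. That reading does not remove the conflict.

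**Which outcome is affected.** Measures gives enrollment as the primary outcome for Objective 1 and verified abstinence for Objective 2. Session content and NRT follow enrollment, so inconsistencies in how they are delivered bear on abstinence and not on enrollment.

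**The case against.** The best defense is that the design is open about what each arm gets. The Background part of the Abstract states the comparison correctly, without preloading. Several sections say plainly that everyone is preloaded, and neither Measures nor Analyses attributes an effect to preloading. On biofeedback, one general section stands against four explicit exclusions, and the fidelity checklist assigns discussion of results to Enhanced Care. The Discussion already concedes the extra contact time and the difficulty of separating components. All of this is true, and it makes the problem mainly one of wording. It does not cure it: the Background says that the three-part bundle is what is evaluated, and the limitation itself is misstated.

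One could add that opt-out enrollment may bring more people in the Enhanced Care arm to treatment, and so to preloading. That would be an effect of opt-out on uptake of a treatment available in both arms. It would not make preloading a component that differs by assignment.

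A reader might draw four stronger conclusions that the document does not support:

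- *That controls will receive biofeedback, with a calculable loss of contrast.* The arm-specific text excludes it, and nothing in the document indicates how often it would happen.
- *That NRT is withheld from Standard Care.* RCT study design only omits it there, whereas Pharmacological support states provision in both arms. What remains is that metabolite-guided titration is described for Enhanced Care alone, so NRT use could differ by arm.
- *That unequal NRT use would corrupt verification through cotinine.* Measures also specifies anabasine, with a cutpoint of 2 ng/mL, to distinguish tobacco use from NRT.
- *That the control arm contradicts Study setting, where counseling and NRT are offered "with varenicline prescribed as needed".* That section describes the existing program. The trial defines its own Standard Care arm openly.

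**Conclusion.** The point stands in two parts. First, one of the three components named in the Enhanced Care bundle is the same in both arms, so no effect of preloading, or of a bundle that includes it, can be claimed, and the stated limitation is wrong on this. This follows from the text and needs no assumption. Second, Counseling approach contradicts the arm descriptions on biofeedback. The harm is conditional: it arises only if the specialist follows that section, it touches abstinence and not enrollment, and its size cannot be given. The NRT statements are a lesser inconsistency, largely an omission. Opt-out versus opt-in enrollment is described consistently, so the enrollment comparison keeps its headline contrast. The changes should be made now, since recruitment is in progress, but they do not alter randomization or the sample.

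**What to change.** 1. In the Abstract (Discussion), the last Background paragraph, and the limitations and closing paragraphs of the Discussion, remove preloading from the tested contrast and from the conclusions. State the contrast as opt-out enrollment with proactive outreach, biofeedback and longer sessions, on a common background of varenicline with preloading. Reword the limitation to match.
2. In Counseling approach, make both mentions of biofeedback specific to Enhanced Care.
3. The fidelity checklist is in a supplement not shown here. Unless it already has such an item, add a yes/no entry for whether LDCT, spirometry or urine results were discussed in a Standard Care session. Report the rate of result discussion by arm.
4. Have the clinical team reconcile the NRT statements in RCT study design, Enhanced Care arm and Pharmacological support. Report NRT use by arm.

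A single table of components by arm would keep the sections in agreement. The cost is text editing, one checklist line and a narrower claim.
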